## Methods

2.

### Study design

2.1.

The study will be a two-armed, phase 2 exploratory RCT to assess the preliminary efficacy, adherence, feasibility and factors affecting outcome of the Rewind Technique versus a waitlist control group (Table 1).

**Table 1. t0001:** Gantt chart illustrating study timeline

[figure not shown]

### Setting

2.2.

Participants will be people with PTSD living in South Wales. Recruitment will primarily occur through University Health Boards in South Wales using approaches that have proved successful in other RCTs run by Cardiff University’s Traumatic Stress Research Group (Lewis et al., 2017; Nollett et al., 2018).

### Sample size

2.3.

While a definitive power calculation is not necessary for a phase 2 exploratory trial, it is nonetheless important to ensure our sample size is appropriate and adequate. We conservatively based this power calculation on the broad range of effect sizes reported for trauma-focused psychological therapies for PTSD. While it is difficult to compare the wide range of effect sizes reported in heterogeneous trials, as meta-analyses demonstrate (Lewis et al. 2020, Mavranezouli et al., 2020), we considered an effect size of 1.45 highly clinically relevant.

Using the Lehr method to give a sample size with 80% power, a 5% significance level and an effect size of 1.5, 15 participants are required in each arm of the trial, with a total number of 30. Estimating a conservative 25% attrition rate, informed by recent similar research (Lewis et al. 2020), we will include 20 participants in each arm of the trial, giving 40 participants in total.

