Some reconsolidation approaches have yielded negative results (Bos, Beckers, & Kindt, 2014; Wood et al., 2015) highlighting the specific limitations which exist around the ability of a therapy to destabilise and modify a traumatic memory. These factors, such as the length of the memory reactivation procedure and the age and context of the traumatic memory, are known as boundary conditions (Treanor, Brown, Rissman, & Craske, 2017) and have complicated the process of translation from experimental into clinical settings. Promising preliminary evidence, however (Adams & Allan, 2018; Utuza, et al., 2012), suggests that if reconsolidation is the mechanism of action for the Rewind technique, that these conditions may have been met.

While trauma-focused psychotherapies (TFCBT, EMDR) have medium to large effect sizes, the therapy requires large amounts of therapist time (Lewis et al. 2020). We expect that Rewind will have a similar effect size, but be more time and cost efficient, delivering a trauma-focused intervention in just a few sessions. Furthermore, as Rewind is relatively simple to deliver it has potential to be delivered by lower intensity therapists and therefore is more easily scalable. Furthermore, evidence of multiple effective therapies also provides treatment choice for people with PTSD, e.g. some individuals may prefer Rewind as it does not require trauma disclosure. Considering this, Rewind may be most suitable as a first-line intervention as part of a stepped care approach.

Given the promise of non-pharmacological approaches to the treatment of PTSD through the mechanism of memory reconsolidation, we aim to undertake a preliminary efficacy RCT to determine if the Rewind Technique is likely to be a good candidate to test against usual care in a future pragmatic efficacy RCT. Our objectives are:

1. To investigate the effect sizes of the Rewind Technique at reducing PTSD symptoms in people with PTSD.

2. To establish whether any symptom improvement is maintained over 16 week follow up.

3. To investigate the impact of the Rewind Technique on symptoms of depression, anxiety and insomnia.

4. To investigate if an efficacy RCT is feasible and indicated.

5. To assess if the Rewind Technique is acceptable to participants with PTSD as measured by a qualitative questionnaire.

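### The stated effect size, power and sample size do not belong together: Lehr's rule at an effect size of 1.5 gives 8 per arm, not 15

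*Protocol article*

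**What the plan says.** Section 2.3 (Sample size) of the protocol article first says that a definitive power calculation is not needed for a phase 2 exploratory trial, but that the size should still be appropriate and adequate. On the basis it says: "We conservatively based this power calculation on the broad range of effect sizes" reported for trauma-focused psychological therapies. On the target it says: "we considered an effect size of 1.45 highly clinically relevant".

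The next paragraph calculates with a different value, using Lehr's method: "80% power, a 5% significance level and an effect size of 1.5, 15 participants are required in each arm of the trial". That makes 30 in total. An allowance of 25% for attrition raises this to 20 per arm, 40 in total.

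Two other places bear on the point. Section 1 (Background and rationale) describes the effects of established trauma-focused therapies as medium to large, without a number, and adds: "We expect that Rewind will have a similar effect size". Section 2.9 (Planned analyses) plans an ANCOVA on continuous outcomes with the baseline value as covariate.

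**The concern.** The section names its method, power, significance level and effect size, so its result can be checked directly. It does not reproduce. The section also gives two target effect sizes in consecutive paragraphs, 1.45 and then 1.5.

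This paragraph is the only justification given for 40 participants. A reader who takes it at face value will believe that 15 evaluable participants per arm reach 80% power only for a difference of about 1.5 standard deviations. The true threshold is about 1.06. What is at stake is a correct account of what the trial can detect, which matters to anyone who later uses its result to plan a larger trial.

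**Working it through.** **Inputs, all from section 2.3:** Lehr's method; 80% power; 5% significance (sidedness not stated; Lehr's rule is two-sided); effect size d = 1.5, with 1.45 named just before; 15 per arm before attrition; 25% attrition. Section 2.7 (Intervention) gives 1:1 allocation.

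**1. The plan's own figure.** Lehr's rule is n per arm = 16/d², where 16 rounds 2 × (1.960 + 0.842)² = 15.7.

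- d = 1.5: 16/2.25 = 7.11, so 8 per arm, 16 in total.
- d = 1.45: 16/2.1025 = 7.61, so 8 per arm, 16 in total.

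The stated 15 per arm (30 in total) is not reproduced.

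**2. Cross-check by other methods, 80% power and 5%.**

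| Method | d = 1.5, per arm | d = 1.45, per arm |
|---|---|---|
| Normal approximation, two-sided | 7 | 8 |
| Exact t, two-sided | 8.06 | 8.54 |
| Exact t, one-sided | 6.30 | 6.68 |
| Exact t, two-sided, with a Wilcoxon efficiency of 0.864 | 9.33 | 9.89 |

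By exact t at d = 1.5, 8 per arm has 79.7% power, so strict rounding up gives 9. No variant comes near 15.

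**3. What would give 15.** At d = 1.5 and two-sided 5%, exact t needs 14.7 per arm for 97.5% power, so 15 per arm matches about 97.5% power rather than 80%. A two-sided level of 1% at 80% power needs 12.1, so 13 per arm, which is still below 15 and contradicts the stated 5%.

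**4. What 15 evaluable per arm provides (unadjusted two-sample t, two-sided 5%).**

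- Power at d = 1.5: 97.7%. At d = 1.45: 96.9%.
- Effect detectable with 80% power: 1.06 by exact t; by Lehr, √(16/15) = 1.03.
- If all 20 per arm are retained, the effect detectable with 80% power is 0.91.

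**5. Attrition step.** 15/0.75 = 20 per arm. This step is correct. Lehr's 8 would have become 8/0.75 = 10.7, so 11 per arm.

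**6. Smaller effects, on assumptions.** The protocol gives no number for medium to large and no correlation between baseline and follow-up CAPS-5. Assume d from 0.5 to 0.8 and correlation r of 0.5 or 0.7. ANCOVA acts roughly as if d were divided by √(1 − r²). At 15 per arm:

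| Assumed d | Unadjusted | ANCOVA, r = 0.5 | ANCOVA, r = 0.7 |
|---|---|---|---|
| 0.5 | 26% | 33% | 46% |
| 0.8 | 56% | 68% | 84% |

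**The case against.** The arithmetic cannot be defended: nothing else in the article rescues 15, and the planned ANCOVA would lower the required number. The case on the other side concerns consequence, and much of it stands.

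The error runs in the safe direction, since the trial has more participants than its stated inputs require. The protocol says that a definitive calculation is unnecessary, and the Discussion says that the trial is not powered to assess effectiveness definitively. The gap between 1.45 and 1.5 may be rounding, and both give 8 by Lehr. None of this makes the stated figures agree, but it lowers the weight of the point.

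A reader might also infer four stronger things that the document does not support.

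- *That the trial is underpowered for the effect it expects.* The protocol gives no number for that effect. The range 0.5 to 0.8 is an assumption, and under the planned ANCOVA power at 0.8 could reach about 84%.
- *That a non-significant result would be misread.* No section makes significance the rule for going on to a further trial. The objectives are to investigate effect sizes and whether an efficacy RCT is feasible and indicated, and the Discussion says that the estimates will inform a later power calculation.
- *That calling the basis conservative is false.* The word is attached to using the broad range of reported effects; the text does not say that 1.5 itself is conservative.
- *That Lehr's total was entered as the per-arm number and doubled.* The total, 32/1.5² = 14.2, does round up to 15, but at 1.45 it is 15.2, which rounds up to 16. This is a possible explanation that the document does not confirm.

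**Conclusion.** The point holds as an arithmetic error in a stated figure. The section's effect size, power and sample size cannot all be true together: its inputs give 8 per arm by Lehr (8 to 9 by exact t), and 15 is nearly twice that. The trial is not short for its stated effect. The power and detectable-effect figures for 15 per arm assume a two-sided test, equal arms and 15 evaluable in each; they are unadjusted, so the planned ANCOVA can only be expected to improve on them.

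No firm conclusion about power at medium-to-large effects follows. On the assumed range of 0.5 to 0.8, power at 15 per arm is 26% to 56% unadjusted and roughly 33% to 84% with ANCOVA at correlations of 0.5 to 0.7.

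The severity is moderate. The paragraph should be corrected because it alone justifies the sample size, but design, endpoint and analysis are unaffected.

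**What to change.** Keep 20 randomised per arm and the 25% attrition allowance. Use one target effect size throughout section 2.3 instead of both 1.45 and 1.5, and state that the test is two-sided. Replace the calculation with one that agrees with itself, for example: *Fifteen evaluable participants per arm give 80% power at two-sided 5% for a standardised difference of about 1.06 (unadjusted t-test), and about 98% power at 1.5.* If 1.45 is the value kept, the second figure is about 97%.

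If power is also quoted for smaller effects, give the assumed effect range and baseline correlation beside it. The unadjusted 26% to 56% should not stand alone, because it does not match the planned ANCOVA.

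The cost is a rewording of one paragraph. It needs no extra participants and no change to the design or analysis.

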### Inclusion/exclusion criteria

2.4.

In order to determine the likely efficacy of the Rewind Technique for people with PTSD presenting to the UK’s National Health Service (NHS) we will adopt a pragmatic approach and employ broad eligibility criteria.

Inclusion criteria will be: adults aged 18 or over who are fluent in English, able to provide informed consent, and who meet DSM-5 criteria for PTSD secondary to a single traumatic event.

Exclusion criteria will be: current psychotic or bipolar disorder, traumatic brain injury, substance dependence, acute suicidal ideation, learning disability, previous or current receipt of an adequate trial of trauma-focused psychological treatment for PTSD, change to the type or dosage of psychotropic medication within one month of baseline assessment. The presence of other mental disorders will be allowed as long as PTSD is the primary condition, and pretreatment comorbidity will be assessed using clinical presentation and self-report.

### Recruitment and consent

2.5.

Potential study participants who are thought likely to fulfil the inclusion criteria for the trial will be asked by a clinician involved in their care if they are willing for their details to be passed on to the research team. Participants will also be recruited via the National Centre for Mental Health (NCMH), a Welsh government-funded research centre (NHS Health Research Authority, 2016), which recruits through primary and secondary mental health services as well as through a variety of media outlets and online advertising strategies. The research team will contact potential study participants and provide them with an information leaflet about the research. After 24 hours they will be asked if they would like any further information or have any queries they would like answered. If potential participants wish to proceed, arrangements will be made to enter them into the study through recruitment screening.

Participants will provide fully informed consent to take part in the study before their initial assessment. The individual taking consent will check that the participant has read and understood the information sheet provided and answer any participant questions that arise. They will check the participant’s understanding that their participation is voluntary and that they are free to withdraw (on a variety of levels) at any time without giving any reason (without their medical care or legal rights being affected), and ask if the participant agrees to their GP being informed of their participation in the study. Data will be handled with full compliance to the General Data Protection Regulations 2016.

### Outcome measures

2.6.

A trained member of the research team, blind to randomization, will conduct all clinical assessments. It is not possible for therapists or participants to be blind to treatment allocation, but participants will be asked not to discuss their allocation with their assessor. An initial telephone screen will confirm that the participant meets the inclusion criteria. To ensure they consistently meet the inclusion criteria, participants will be asked to monitor their symptoms for two weeks, at which point we will take informed consent, collect baseline demographic data, outcome measurements, reassess eligibility, and then randomise eligible individuals to one of two groups using a computer programme: the Rewind Technique immediately or a waitlist for eight weeks followed by the Rewind Technique. We will monitor change in PTSD, depressive and anxiety symptoms using the PTSD Checklist (PCL-5), Patient Health Questionnaire (PHQ-9), and General Anxiety Disorder-7 (GAD-7) at the start of each treatment session. Follow-up and repeated collection of outcome data will occur 8 and 16 weeks post-randomisation.

The primary outcome of PTSD symptom severity, and PTSD diagnosis will be measured by trained assessors using the Clinician Administered PTSD Scale for DSM-5 (CAPS-5) (Weathers et al., 2018). The CAPS-5 is widely referred to as the gold standard in PTSD assessment, demonstrating high internal consistency (α =.88) and strong test-retest reliability (к = .83) (Weathers et al., 2018). Measuring DSM-5 PTSD allows comparability with previous psychological therapy RCTs.

Secondary outcomes, collected at 8 and 16 weeks will include:

The PTSD Checklist (PCL-5), a validated and widely used self-report measure for DSM-5 PTSD symptoms (Ruggiero, Del Ben, Scotti, & Rabalais, 2003).

The International Trauma Questionnaire (ITQ), a validated self-report measure for ICD-11 PTSD and complex PTSD (Cloitre et al., 2018).

The Patient Health Questionnaire-9 (PHQ-9), a validated and widely used self-report measure for assessing DSM-5 depressive symptoms (Kroenke, Spitzer, & Williams, 2001).

The Generalised Anxiety Disorder Assessment-7 (GAD-7), a validated and widely used self-report measure for assessing symptoms of generalised anxiety disorder (Spitzer, Kroenke, Williams, & Lowe, 2006).

The Insomnia Severity Index (ISI), a validated and widely used self-report measure for symptoms of insomnia, such as prolonged sleep latency and effects on functioning, over the past month, using a five-point Likert scale (Morin, Belleville, Bélanger, & Ivers, 2011).

The five-level EQ-5D (EQ5D-5 L), a validated and widely used self-report measure for health-related quality of life. It is recognised by NICE as such and is frequently used in health economic analyses (EQ-5D, 2017).

An intervention acceptability questionnaire to gauge acceptability and feasibility of the intervention, as perceived by the participant, will be completed at the end of the final session and returned to a member of the research team in a sealed envelope. Feasibility will be partly assessed through dropout numbers.

The prominence of re-experiencing symptoms will be assessed through a score of ≥3 on CAPS-5 items B1, B2 or B3).

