## Abstract

**Background:** An increasing body of research highlights reconsolidation-based therapies as emerging treatments for post-traumatic stress disorder (PTSD). The Rewind Technique is a non-pharmacological reconsolidation-based therapy with promising early results, which now requires evaluation through an RCT.

**Objectives:** This is a preliminary efficacy RCT to determine if the Rewind Technique is likely to be a good candidate to test against usual care in a future pragmatic efficacy RCT.

**Methods:** 40 participants will be randomised to receive either the Rewind Technique immediately, or after an 8 week wait. The primary outcome will be PTSD symptom severity as measured by the Clinician-Administered PTSD Scale for DSM5 (CAPS-5) at 8 and 16 weeks post-randomisation. Secondary outcome measures include the PTSD Checklist (PCL-5), International Trauma Questionnaire (ITQ), Patient Health Questionnaire (PHQ-9), the General Anxiety Disorder-7 (GAD-7), Insomnia Severity Index, the Euro-Qol-5D (EQ5D-5 L), the prominence of re-experiencing specific symptoms (CAPS-5) and an intervention acceptability questionnaire to measure tolerability of the intervention.

**Conclusions:** This study will be the first RCT to assess the Rewind Technique. Using a cross-over methodology we hope to rigorously assess the efficacy and tolerability of Rewind using pragmatic inclusion criteria. Potential challenges include participant recruitment and retention.

**Trial registration:** ISRCTN91345822

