## Background and rationale

1.

Post-traumatic stress disorder (PTSD) is a common mental illness occurring after a traumatic event, with symptoms of re-experiencing, hyper-arousal, negative alterations in cognition and mood, and avoidance. It has been estimated that between 1.1% and 2.9% of EU adults suffer from PTSD (Wittchen et al., 2011) and the prevalence of PTSD in high-risk populations such as those exposed to certain types of interpersonal trauma, mass conflict and displacement are estimated to be much higher (Kessler et al., 2017; Steel et al., 2009). PTSD is associated with substantial physical and psychiatric co-morbidity, for example type 2 diabetes, ischaemic heart disease, somatic symptom disorder, substance abuse and suicide (Roberts et al., 2015) and research suggests that current psychological and pharmacological treatments remain ineffective in a substantial proportion of those with PTSD (Olff et al., 2019, Lewis et al. 2020). Trauma-focused psychological therapies in the form of individual trauma-focused cognitive behavioural therapy (TFCBT) and eye movement desensitisation and reprocessing (EMDR) are currently the most effective treatments for PTSD symptoms with pharmacological approaches effective but to a lesser degree (National Institute for Health and Care Excellence (NICE), 2018, Bisson et al. 2019). Sadly, many people with PTSD remain symptomatic, despite evidence-based treatment, partially due to high drop out rates in trauma-focused therapies, which appear particularly difficult to tolerate (Lewis et al. 2020). There is an urgent need to develop more effective treatments (Olff et al., 2019), which are shorter in duration and less emotionally distressing (Lewis et al. 2020).

The positive outcomes of recent studies of novel treatments have raised interest in the mechanism and study of memory reconsolidation and further work in this area is merited to establish the exact mechanism of action (Brunet et al., 2018; Gray, Budden-Potts, & Bourke, 2017). As memory reconsolidation has been specifically targeted by some novel treatments (Gray et al., 2017) which have many similarities to the Rewind technique (the psychological intervention assessed here) we will consider reconsolidation theory in detail below.

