### Intervention

2.7.

*The Rewind Technique –* This will comprise up to three 60-minute sessions following a protocol developed by [name] (Muss, 1991) which has been modified by [name] and the research team following feedback from therapists. The intervention will be administered by experienced and trained psychological therapists under the supervision of [name] and the Cardiff and Vale University Health Board Traumatic Stress Service. The participant will be introduced to the technique and the theory behind it before being asked to imagine he/she is in a cinema watching a film of her/his traumatic event as if it had been captured on CCTV. Rather than the film start at the trauma itself the person with PTSD is told the film starts just before the traumatic event took place and is then followed by the regular intrusive recall which includes all the images, sounds and smells plus (if this is part of the regular recall) what could have happened next but didn’t. Once the recall ends, the sufferer is (metaphorically) invited to enter the screen and at that point the film is rewound at speed back to the exact starting point (where all was well before the trauma). The forward part of the process of recalling the trauma should not take longer than 2 minutes, the rewind part about 10 seconds. This usually requires the person with PTSD to practise the technique a few times before feeling confident it is being undertaken as intended.

*Wait list* – The wait list group will receive no intervention for 8 weeks after randomisation, at which point they will then receive the Rewind Technique in the same manner as the immediate treatment group.

Participants will be randomised to receive either the Rewind Technique or wait list using a 1:1 ratio.

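### The acceptability questionnaire is collected once, at the close of the last session, so participants who simply stop attending are likely to be missed and tolerability may look too favourable

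*Protocol article*

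**What the plan says.** The abstract lists among the secondary measures "an intervention acceptability questionnaire to measure tolerability of the intervention". Objective 5, at the end of Background and rationale, is "To assess if the Rewind Technique is acceptable to participants with PTSD as measured by a qualitative questionnaire". Both therefore rest on one instrument.

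Section 2.6 (Outcome measures) fixes when it is collected: it "will be completed at the end of the final session and returned to a member of the research team in a sealed envelope". The next sentence adds: "Feasibility will be partly assessed through dropout numbers". The lead-in to the same list reads "Secondary outcomes, collected at 8 and 16 weeks will include".

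Three other places bear on the point:

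- Section 2.7 (Intervention) allows up to three sessions, so the number can differ between participants. The waitlist arm receives Rewind after week 8, so participants in both arms are due to be asked for a rating.
- Section 2.3 (Sample size) plans for loss: "Estimating a conservative 25% attrition rate, informed by recent similar research".
- Background and rationale explains why many patients stay symptomatic despite treatment: "partially due to high drop out rates in trauma-focused therapies, which appear particularly difficult to tolerate".

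The measures taken at the start of each session under section 2.6 (PCL-5, PHQ-9, GAD-7) record symptoms, not acceptability.

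**The concern.** Whether a participant is asked about tolerability depends on whether they are still attending, and attendance may itself depend on tolerability. Someone who finds the first or second session too distressing and does not come back is not present when the form is handed out. The ratings then come mainly from those who tolerated the treatment.

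This matters because tolerability is a main argument for Rewind. The Discussion suggests that it may be easier to bear than existing therapies, and makes acceptability one of the grounds for deciding whether a larger trial is indicated. The Discussion also expects that avoidance and anxiety will make retention difficult, so the affected group may not be empty. A rating that was never sought at the time is hard to recover later.

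**Working it through.** **1. The plan's own attrition figure.** Section 2.3 starts from 15 per arm and allows for 25% attrition:

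15 / (1 − 0.25) = 20 per arm, 2 × 20 = 40 in total.

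This reproduces the stated 20 and 40. At that rate, 0.25 × 40 = 10 participants would be lost from the trial. Ten is only an upper guide to the number missing from the questionnaire because of intolerability. The 25% is loss from the trial for any reason, and some waitlist participants may leave before they have had any Rewind to rate.

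**2. Who can be reached under the stated rule.**

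| Participant | Form completed as written? |
|---|---|
| Attends all planned sessions | Yes |
| Says during a session that they are stopping | Possibly, if that session is treated as their last |
| Leaves a session and does not return | Unlikely: nobody knew at the time that it was the last |
| Leaves the waitlist before any Rewind session | No, but has nothing to rate |

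The third row is the gap.

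**3. Direction.** Let *s* be the share of those starting Rewind who stop early and give no form, *p_f* the share of finishers who find it acceptable, and *p_s* the share of early stoppers who do.

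- Observed result: *p_f*
- Result among all who started: (1 − *s*) × *p_f* + *s* × *p_s*
- Overstatement: *s* × (*p_f* − *p_s*)

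The overstatement is positive when stoppers rate Rewind worse than finishers, zero when they rate it the same, and negative otherwise. The Background's remark on dropout and tolerability makes the first case the expected one.

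**4. Size, on assumed values.** The documents give no acceptability rate and no rate of early stopping from Rewind. All values of *s*, *p_f* and *p_s* below are assumptions; 25% is borrowed from the attrition allowance.

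| *s* | *p_f* | *p_s* | Overstatement |
|---|---|---|---|
| 10% | 70% | 0% | 0.10 × 0.70 = 7 points |
| 10% | 90% | 0% | 0.10 × 0.90 = 9 points |
| 25% | 70% | 0% | 0.25 × 0.70 = 17.5 points |
| 25% | 90% | 0% | 0.25 × 0.90 = 22.5 points |
| 25% | 80% | 50% | 0.25 × 0.30 = 7.5 points |
| any | any | equal to *p_f* | 0 points |

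The rows with *p_s* = 0% are the worst case for each pair of *s* and *p_f*. The calculation also supposes a yes/no rating, which the documents do not describe.

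**The case against.** The case against is substantial, and much of it stands.

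- **A reader might infer that only those who complete all three sessions are asked.** The text does not say so. With up to three sessions, the last one can be each participant's own, and someone who announces that they are stopping could fill in the form. This narrows the gap to people who leave without notice; it does not close it.
- **A reader might infer that the plan cannot detect poor tolerability, or must favour Rewind.** Neither follows. Dropout numbers are reported and heavy early loss would be visible; finishers can also rate Rewind poorly. But the counts are assigned to feasibility and do not separate distress from early improvement or unrelated reasons.
- **A reader might take 25% as the share who stop Rewind early, or put a single figure on the bias.** The 25% is an allowance for trial attrition, and objective 5 calls the instrument qualitative. No acceptability percentage or threshold appears anywhere.
- **A reader might see a contradiction between the lead-in's weeks 8 and 16 and the questionnaire's own timing.** The specific statement governs, and nobody would ask an untreated waitlist participant to rate Rewind at week 8. This is editorial.
- **Follow-up of missing forms may be set out in a fuller protocol.** That is possible, and its absence here is not in itself the point. The article does, however, state a collection point, and following that rule selects respondents partly on the property being measured.

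The intention-to-treat statement in section 2.9 does not answer the point, because analysing everyone randomised cannot supply a form that was never collected.

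**Conclusion.** The concern holds in a limited form. As written, the only measure of tolerability is likely to miss participants who do not return after an earlier session, and on the protocol's own reasoning its result is likely, but not certain, to look too favourable. The documents do not determine the size: the assumption-based range runs from zero, where stoppers rate like finishers, to 22.5 points at 25% early stopping in the worst case considered, and to 9 points at 10%. The issue affects objective 5 and one input to the decision on a further trial. It does not touch the CAPS-5 primary comparison. It is a cheap improvement worth making, not a flaw that undermines the trial.

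**What to change.** In section 2.6, state that the questionnaire and the reason for stopping will be sought from everyone who attended at least one Rewind session:

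- at the last session; or
- if sessions stopped early, by post or phone around the next scheduled follow-up (week 8 for the immediate arm, week 16 for the waitlist arm).

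A team member other than the blinded assessor should handle these contacts, since a conversation about the treatment would reveal allocation. Participants should remain free not to reply or give a reason.

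Report acceptability beside three numbers: those who started Rewind, those who stopped early, and those who returned the form. Do not count unreturned forms as unfavourable unless the questionnaire yields a binary rating; some people will have stopped for unrelated reasons. In the same edit, exempt this item from the week 8 and week 16 lead-in.

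The cost is a sentence or two and a few extra forms or calls. Some early stoppers will not respond, so the gap will shrink rather than vanish, and the result may be less favourable.
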